On the morning of the second full challenge phase day (challenge phase day 2; day 41 ± 3 after first immunization), all remaining eligible and consenting subjects will receive a dose of viable, egg-grown A/Panama/2007/99 by intranasal drops. The challenge inoculum will be selected so as to achieve illness and infection rates of 50 - 70% in the subjects who received placebo during the immunization phase.

Between challenge phase day 2 (p.m.) and challenge phase day 9 (p.m.), subjects will complete a standard diary card of symptoms of influenza twice each day. During these days, oral temperatures will be measured at least four (4) times daily, and contents of the diary cards will be elicited by a directed interview and recorded, approximately every twelve (12) hours. Once per day, at approximately 24 hour intervals, each subject will have a directed physical examination of the ears, nose, throat, and chest. Once per day, and at approximately 24 hour intervals, each subject will have a nasal wash **and throat swab for detection and / or quantitation of influenza virus using culture, antigen detection or molecular biology techniques.** Tissue counts and weights will be collected throughout challenge as a surrogate of disease severity. Beginning on the morning of challenge phase day 8, each subject will begin five (5) days of twice-a-day treatment with oseltamivir to ensure termination of virus shedding. Amantidine will be available as an alternative treatment should intolerance to oseltamivir be a problem for any subject. Subjects will be re-evaluated in the p.m. hours of challenge phase day 9, and, if illness has resolved, be discharged. Any subject who is either febrile (oral temperature ≥ 37.9º C) or has persistent symptoms of grade 2 or greater will be retained in the facility for an additional 24 hours. Subjects remaining symptomatic will be referred for appropriate medical care. (Illness following inpatient influenza challenge is typically somewhat milder than community- acquired influenza, and short lived. This inpatient period, even without antiviral treatment, extends beyond the typical duration of virus shedding in this model.)

All subjects (challenged and unchallenged) will return between challenge phase days 20 to 30 and be queried regarding adverse events or changes in concomitant medications since discharge; a physical examination will be performed as needed to evaluate complaints and a follow-up ECG will be obtained if any abnormalities were noted at discharge. Serum and nasal wash specimens will be obtained for specific antibody determinations and the subjects discharged from the study.

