Safety and immunogenicity data continue to be analyzed, but are in general consistent with prior experience. Approximately 70% of both one- and two-dose vaccinees had signficant aserum HAI responses. A per-protocol analysis of the challenge study data revealed influenza-like illness in 66.7% of challenged placebo recipients, 62.5% of challenged one-dose recipients (6.3% efficacy), and 31.8% of challenged two-dose recipients (52.3% efficacy); yielding a chi2 p value of 0.041 for the 3 x 2 table and a p value of 0.021 for trend with number of vaccine doses. However, examination of the data has revealed that physician exam findings were non-contributory with one exception: pharyngitis; and that the definition of pharyngitis as applied by the study physicians led to fulfillment of the criteria for “illness” in a number of essentially asymptomatic subjects. In addition, the calibration of the disposable digital thermometers used to monitor temperature was questioned, as these yielded mean baseline temperatures just over 36ºC. Setting aside physician-observed pharyngitis and using a definition of fever based on the baseline mean + three standard deviations revealed a similar, but much stronger, efficacy trend in the data: 57.1% illness in placebo recipients; 45.8% illness in one-dose recipients (19.8% efficacy); and 4.5% illness (92.1% efficacy) in two-dose recipients (chi2 p value of 0.0007 for the 3 x 2 table and a p value of 0.0003 for trend with number of vaccine doses). An analysis based on laboratory-confirmed influenza illness (which requires illness and either isolation of influenza virus or a four-fold rise in reciprocal HAI titer across the challenge interval) demonstrates 65% efficacy in the one-dose group and 100% in the two-dose group. Because the sensitivity of influenza culture has proved poor for this strain however, this analysis remains preliminary pending data from molecular detection methods and immunoflouresence studies.

The current study is being undertaken to: a) confirm the efficacy of the two-dose regimen at a 30 μg dose level, b) re-examine the efficacy of the one-dose regimen at the 30 μg dose level with refined illness criteria, and c) examine the possible efficacy of a two-dose regimen at a 15 μg dose level, which is also highly immunogenic.

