## 6.6 Accountability for Study Drugs:

The Investigator or a designee is responsible for maintaining complete drug inventory records accounting for receipt, storage, dispensation, and final disposition using forms supplied by (or local equivalents approved by) ID Biomedical. These records will be reviewed by ID Biomedical representatives. At the conclusion of the trial all vials of study drugs, used and unused, and all metered dose pumps will be returned to the sponsor.

6.7 Challenge Virus:

The challenge virus is A/Panama/2007/99 (H3N2) lot I B 44/3 produced in eggs by Berna Biotech Ltd. This material is sterile and mycoplasma-free. The titer of this virus as provided by the manufacturer is 108.46 egg ID50 / mL, and it is provided in cryovials. Prior to challenge, the virus will be diluted to the predetermined desired challenge inoculum in sterile isotonic phosphate-buffered saline.

6.8 Storage of Challenge Virus:

Challenge virus should be stored at ≤ - 70º C in a secured freezer until use. Vials should be thawed just prior to dilution. Once thawed and entered, vials of stock virus should NOT be reused for human studies.

6.9 Disposal of Challenge Virus:

Used challenge virus stock vials and dilutions will be disposed of according to Retroscreen Ltd’s SOPs for the destruction of biohazardous waste.

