- A  4-fold increase in serum A/Panama/2007/99 HAI antibody titer between day 39 ( 3) and the final follow-up visit, and absent clinical disease suggesting influenza between discharge from the isolation unit and the final follow-up visit.

9.3.7 Laboratory-confirmed Influenza Illness:

A subject will be deemed to have laboratory-confirmed influenza illness if he/she meets the definitions for BOTH of:

- Influenza infection, and
- Illness (Any).

9.3.8 Analysis:

9.3.8.1 Power Considerations:

The analysis will consider both binary outcomes (e.g., illness vs. no illness; virus shedding vs. no virus shedding, etc.) and continuous outcomes (e.g., treatment group mean temperatures, tissue counts, peak viral shedding and shedding AUC, etc.). The variability, and potential magnitudes of the differences in the latter are *a priori* unknown. However, the virus challenge inoculum will be selected to yield *approximately* 50 - 60%, based on past experience, of the binary outcome “any illness.” (Closer control of this rate is difficult to ensure.) Assuming that a minimal efficacy level of 70% (where efficacy = [rate controls -ratetreated ] x 100 / rate controls) is of interest to justify further development of a given dose or formulation, it is possible to calculate that a group size of 28 will yield ≥ 0.80 power to detect a ≥ 70% reduction in the rate of the binary outcome “any illness.”

9.3.8.2 Analyses:

The analysis concerns between-group comparisons of the four cross-over groups regarding clinical and immunologic binary outcomes. Alternative definitions provide six binary clinical outcomes (fever, upper respiratory illness, lower respiratory illness, systemic illness, illness [any], and illness + infection) that can be compared between groups by chi-square tests. More flexible analyses use logistic regression (SAS PROC LOGISTIC) with the presence or absence of influenza, separately for each definition, as the outcome. Covariates are cross-over study group, age, gender, race, and, for some models, titers after vaccinations 1 and 2.

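### Sections 5.2 and 9.3.8.1 give the challenge inoculum two different target attack rates, and the 0.80 power claim needs restating across one agreed range

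*Protocol*

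**What the plan says.** Two sections of the protocol state how the challenge inoculum is chosen.

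- Section 5.2 (Challenge Phase): "The challenge inoculum will be selected so as to achieve illness and infection rates of 50 - 70% in the subjects who received placebo".
- Section 9.3.8.1 (Power Considerations): "the virus challenge inoculum will be selected to yield" approximately "50 - 60%, based on past experience, of the binary outcome" any illness. It adds in parentheses: "Closer control of this rate is difficult to ensure".

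Section 6.7 gives the titer of the virus stock and says that "the virus will be diluted to the predetermined desired challenge inoculum", without stating the quantity.

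The power statement follows directly on the 9.3.8.1 target. "Assuming that a minimal efficacy level of 70"% is worth detecting, the section says, "a group size of 28 will yield ≥ 0.80 power to detect a ≥ 70% reduction in the rate of the binary outcome" any illness.

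Three other places bear on this. Section 9.0 sets two-sided tests at 0.05 and says the chi-square tests are exact. Section 4.1 enrolls about 28 per group but expects only about 25 per group to be challenged. Sections 9.3.5 to 9.3.7 define illness, infection, and illness with infection as separate outcomes.

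**The concern.** The target attack rate is the only basis that the protocol states for the challenge inoculum. It also sets the placebo event rate, which largely determines the power for any illness. A quantity with that role should have one value. Here it has two upper limits and two descriptions of the outcome, and both sentences are written as the selection rule. This is therefore not a design target set beside a separate planning assumption.

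The outcome matters as well as the limit. A reader of 5.2 would expect the infection rate to be part of the target, while a reader of 9.3.8.1 would not. Section 1.0 reports no placebo infection rate from the earlier challenge study and says that culture performed poorly for this strain. Section 9.3.6 accepts culture, antigen detection or molecular methods. An infection target therefore depends on the assay in a way that an illness target does not.

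The question for power is whether the stated figure holds over whichever range is adopted.

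**Working it through.** **The two targets side by side**

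| | Section 5.2 | Section 9.3.8.1 |
|---|---|---|
| Lower limit | 50% | 50% |
| Upper limit | 70% | 60% |
| Outcome | illness and infection | any illness |
| Wording | plain range | approximate; close control said to be difficult |

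For illness, 50-60% lies wholly inside 50-70%. An inoculum that meets the 9.3.8.1 range also meets the 5.2 illness range. The reverse fails only between 60% and 70%.

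The outcome in 5.2 can be read in two ways. It may mean an illness rate and an infection rate, in which case 9.3.8.1 omits infection. Or it may mean the combined outcome. In that case the rate of any illness is at least as high as the combined rate, so power for any illness is not reduced.

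**Inputs for power**

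- Placebo rate p: 50% to 70% (5.2 and 9.3.8.1).
- Treated rate: 0.30p, from the 70% reduction in 9.3.8.1. This gives 15%, 18% and 21% at p = 50%, 60% and 70%.
- Two-sided 0.05, no multiplicity correction, exact tests (9.0).
- n per group: 28 (9.3.8.1) or about 25 challenged (4.1).

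**Step 1: reproduce the plan's figure.** The pooled normal approximation is

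power = Φ{ [ (p₁ − p₂)√n − 1.96√(2p̄(1 − p̄)) ] / √(p₁(1 − p₁) + p₂(1 − p₂)) }.

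With n = 28, p₁ = 0.50, p₂ = 0.15 and p̄ = 0.325:

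- (p₁ − p₂)√n = 0.35 × 5.292 = 1.852
- 1.96√(2 × 0.325 × 0.675) = 1.96 × 0.662 = 1.298
- √(0.25 + 0.1275) = 0.614
- power = Φ(0.554 / 0.614) = Φ(0.90) = 0.816

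The same formula gives 0.919 at 60% and 0.976 at 70%. The stated 0.80 with 28 per group reproduces over both ranges by this method.

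**Step 2: use the test that the plan names.** Exact power is the sum, over all pairs (x, y) of event counts, of Bin(x; n, p) × Bin(y; n, 0.30p) wherever the two-sided Fisher p-value is at most 0.05. With equal group sizes the null distribution of the table is symmetric, so Fisher's test and the exact chi-square test give the same p-value.

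| Placebo rate | Treated rate | n = 28, approximation | n = 28, exact | n = 25, approximation | n = 25, exact |
|---|---|---|---|---|---|
| 50% | 15% | 0.816 | 0.752 | 0.769 | 0.676 |
| 60% | 18% | 0.919 | 0.871 | 0.885 | 0.834 |
| 70% | 21% | 0.976 | 0.946 | 0.959 | 0.936 |

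With the exact test, 0.80 is reached from a placebo rate of about 54% with 28 per group and about 58% with 25.

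**Step 3: attribute the shortfall.** At 50%, the exact test lowers power from 0.816 to 0.752 with 28 per group. Going from 28 to 25 lowers it further to 0.676. The choice between the two ranges changes nothing at 50%, because both start there. The added stretch from 60% to 70% only raises power.

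**The case against.** The strongest reply is that this is a loose upper limit in a quantity that nobody can control closely, and 9.3.8.1 says so. With 25 challenged placebo recipients, the standard error of an observed 60% rate is √(0.6 × 0.4 / 25) = 0.098. That is about as wide as the whole gap between 60% and 70%, so the observed rate could not show which target had been used. The ranges are nested, the floor is common, and 5.2 may simply add an infection rate that 9.3.8.1 had no need to mention. All of this stands, and it keeps the point small. It does not make the two sentences agree on the upper limit or on whether infection is part of the target.

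Three stronger readings are tempting, and the protocol does not support them.

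- A reader might infer that the inoculum is aimed at one rate and the power at another. Section 9.3.8.1 ties its power statement to an inoculum target in adjacent sentences. The inoculum has two stated targets, and the power uses one of them.
- A reader might set the earlier study's results against the ranges, since that study "revealed influenza-like illness in 66.7% of challenged placebo recipients", which is above 60%, and then 57.1% on re-reading. Section 1.0 itself questions the higher figure, citing the pharyngitis criterion and the thermometer calibration. The 57.1% lies inside both ranges, so these rates do not show that the targets conflict in practice.
- A reader might infer from 6.7 that the inoculum was never fixed. That section calls it predetermined, so the quantity may stand in another document.

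It is also fair to say that 25 is approximate. Section 5.2 admits all eligible and consenting subjects, so the number challenged could be nearer 28. That is why both columns are shown. With 28, the exact test still gives 0.752 at a 50% rate.

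**Conclusion.** The contradiction stands, as a minor one. One selection rule appears with two upper limits and two outcomes, and the passages must be reconciled. The mismatch does not itself reduce the minimum power, and it does not show the stated 0.80 to be miscalculated: 28 per group gives 0.816 at 50% by the usual approximation.

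The power sentence is nevertheless too unqualified for the plan's own exact tests and its own expected number challenged. For a 70% reduction, power runs from about 0.68 at a 50% placebo rate to 0.83 at 60% and 0.94 at 70% with 25 per group, or 0.75, 0.87 and 0.95 with 28. The shortfall near 50% would remain if both sections carried the same range.

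These figures assume equal groups, a pairwise comparison of one active group with placebo, a reduction of exactly 70%, and no multiplicity correction, as section 9.0 states.

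**What to change.** 1. Reconcile 5.2 and 9.3.8.1 to a single target range for a single named outcome as defined in section 9.3. Say whether infection is part of the target. If it is, give it its own stated rate. The choice of range and of inoculum is for the sponsor and investigator.
2. In 9.3.8.1, replace the unqualified 0.80 with power across the agreed range, for the number expected to be challenged and the exact test named in 9.0. The exact columns of the table above cover 50% to 70% for 25 and 28 per group.

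The cost is two edited sentences and a short power table, with no added subjects, visits or procedures.

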# 6.0 Investigational Supplies:

## 6.1 Study Drugs:

Proteosome-trivalent influenza vaccine (*PINK LABEL*): a sterile, colorless to yellowish opalescent liquid containing 150  30 g / mL of hemagglutinin (HA) from each of A/New Caledonia /20/99 (H1N1), A/Panama/2007/99 (H3N2), and B/Shangdong/7/97 viruses in 10 mM Na/K phosphate-buffered isotonic saline, pH 7.4, with 0.01% thimerosal. Non-hemagglutinin viral proteins are also present. The virus components are formulated with outer membrane proteins (OMP) of *Neisseria meningitidis* strain 8047, at an initial ratio of OMPs to HA of 4:1. The overall total protein to hemagglutinin ratio in the final vaccine product is 2.5 – 5:1 (varies slightly with viral strain and non-hemagglutinin protein losses during the complexing process). The vaccine also contains trace amounts of egg proteins. The vaccine is delivered in 3 mL borosilicate glass vials containing **an 0.9** mL fill.

Phosphate-buffered normal saline diluent/placebo (*WHITE LABEL*): a sterile, colorless liquid comprising 10 mM Na/K phosphate-buffered isotonic saline, pH 7.4, with 0.01% thimerosal, delivered in 20 mL borosilicate vials with a 10 mL fill.

## 6.2 Delivery System for Study Drugs:

Valois VP3/140 nasal spray pumps comprising a screw-top vial, an actuator, and a nose piece will be supplied. These devices deliver a metered dose of 140 mL of liquid as an atomized spray with each full depression of the actuator. Delivery of the test article volume by this device has been shown to be  5% of nominal volume with each discharge, and median droplet size in the spray is 40 – 50 m.

## 6.3 Storage Requirements for Study Drugs:

Proteosome-trivalent influenza vaccine should be stored at a controlled temperature of 5  3° C in a secured refrigerator until use. It should NOT be frozen. The vaccine should be used within eight (8) hours of dilution of the stock material and within four (4) hours of removal from refrigeration. While the vaccine contains thimerosal, stock vaccine vials are NOT intended for repeated use over multiple days. Thus, while several doses may be prepared from a single vial of stock vaccine on a given day, residual contents of an opened vial must NOT be used thereafter.

Phosphate-buffered saline should be stored at room temperature away from direct light. Once opened, the contents of a vial may be used for up to eight (8) hours, but residual contents must NOT be used thereafter.

## 6.4 Test Article Dose Preparation:

### 6.4.1 Randomization / Immunization Phase Day 0:

On Study Day 0, the investigational pharmacist (or another unblinded member of site staff who is designated to serve as pharmacist and will have NO involvement whatever with any clinical outcome measurement) will be provided with each eligible, and consenting subject’s initials, subject ID number (SID), and gender. The investigational pharmacist will use the gender-specific randomization list provided by the sponsor to assign the next available randomization code and determine treatment assignment. For each subject randomized, a label bearing the subject’s SID, initials, and randomization code (a two-digit code that does not itself, in the absence of the unblinded treatment list, reveal treatment assignment) will be prepared and affixed to a metered dose pump. In addition, the SID will be transcribed onto the Treatment Group Enrollment Log. The investigational pharmacist will then prepare the appropriate test article for each subject.

For Immunization Phase Day 14 doses, the investigational pharmacist will consult the Treatment Group Enrollment Log to confirm the appropriate treatment group for each subject, and hence the appropriate test article, and then prepare a label bearing the subject’s SID, initials, and randomization code and affix it to a metered dose pump.

### 6.4.2 Preparation of Individual Test Article Doses:

A test article dose will be prepared for each subject to be dosed by placing a total of 0.9 mL of appropriately diluted active vaccine or placebo/diluent, as dictated by the treatment group assignment, into the vial of the previously labeled metered dose pump, after which the actuator and nose piece will be assembled to the pump. Since the target concentrations of each of the three HA species in the vaccine are approximately equal, dosing and dilution will be based on the mean HA concentration in the trivalent (i.e., the average of the concentrations of the three different HAs). Detailed instructions and dose preparation worksheets are provided as Appendix A. After assembly of the pump, the pharmacist will hold the metered dose pump upright, gently swirl once again, remove the nosepiece and then the safety collar, and firmly and fully depress the actuator three (3) times to prime the pump. The collar and then the nosepiece cover will be replaced after priming, and the labeled, filled, and primed pump will be delivered to the clinic.

After test article preparation is completed for a given day, any opened stock vaccine and/or saline placebo vials will be restoppered and retained for retrieval by an ID Biomedical representative.

## 6.5 Test Article Dose Administration:

All study drugs are to be administered under the supervision of the Investigator or a qualified physician subinvestigator / study doctor designated to ID Biomedical in writing prior to the trial and trained in both the protocol and contents of the Investigators’ Brochure. Under no circumstances will the Investigator allow study drugs to be used other than as directed by this protocol.

Test articles will be administered as follows:

 The nosepiece cover will be removed, and then the safety collar.

- The nose piece of the metered dose pump will be placed in the subject’s right nostril while the subject occludes the left.

 As the subject gently inhales through the nose, the actuator will be firmly and fully depressed.

 The nose piece of the metered dose pump will be placed in the subject’s left nostril while the subject occludes the right.

- As the subject gently inhales through the nose, the actuator will be firmly and fully depressed.

 The used pump will be retained for drug accountability and eventual return to the sponsor.

## 6.6 Accountability for Study Drugs:

The Investigator or a designee is responsible for maintaining complete drug inventory records accounting for receipt, storage, dispensation, and final disposition using forms supplied by (or local equivalents approved by) ID Biomedical. These records will be reviewed by ID Biomedical representatives. At the conclusion of the trial all vials of study drugs, used and unused, and all metered dose pumps will be returned to the sponsor.

6.7 Challenge Virus:

The challenge virus is A/Panama/2007/99 (H3N2) lot I B 44/3 produced in eggs by Berna Biotech Ltd. This material is sterile and mycoplasma-free. The titer of this virus as provided by the manufacturer is 108.46 egg ID50 / mL, and it is provided in cryovials. Prior to challenge, the virus will be diluted to the predetermined desired challenge inoculum in sterile isotonic phosphate-buffered saline.

6.8 Storage of Challenge Virus:

Challenge virus should be stored at ≤ - 70º C in a secured freezer until use. Vials should be thawed just prior to dilution. Once thawed and entered, vials of stock virus should NOT be reused for human studies.

6.9 Disposal of Challenge Virus:

Used challenge virus stock vials and dilutions will be disposed of according to Retroscreen Ltd’s SOPs for the destruction of biohazardous waste.

